## Statistical methods

### Statistical methods for primary and secondary outcomes {20a}

All endpoints will be analyzed in the modified intention to treat (mITT) population, defined as randomized patients who are still alive without having emigrated or left the study after 2 and 5 years.

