#### Secondary outcomes

The secondary outcomes will be analyzed using ordinal regression models, adjusted for sex. In addition, each secondary endpoint will be dichotomized and analyzed using logistic regression. The dichotomization will be done by comparing baseline and follow-up data, either based on MCID when applicable or else by defining success as an improvement from baseline. All secondary endpoints will be analyzed at 1, 2, and 5 years of follow-up, but not until the study is closed.

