### Methods in analysis to handle protocol non-adherence and any statistical methods to handle missing data {20c}

Dropouts may be one out of two entities: (1) the participant actively leaves the study or (2) the participant has died or does not show up on follow-ups for unclear reasons. In case 1, the participant will not be part of the study anymore and data will not be retrieved from other information sources. In case 2, information about living participants will be retrieved from the medical records, radiographs, and the Swedish patient registry. In case 2, missing PROMs will be imputed using multiple imputation [44]. Reoperations, adverse events, and radiographs will not be imputed.

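### One analysis set defined by survival and retention at 2 and 5 years serves all endpoints, so it does not fit the 1-year analyses, 5-year adverse events or 5-year mortality

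*Protocol article*

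**What the plan says.** **Analysis set.** The protocol article, *Statistical methods for primary and secondary outcomes {20a}*, gives one rule: "All endpoints will be analyzed in the modified intention to treat (mITT) population". Its members are "randomized patients who are still alive without having emigrated or left the study after 2 and 5 years". The abstract repeats the definition.

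**Time points.** Under the same heading, *Secondary outcomes* states: "All secondary endpoints will be analyzed at 1, 2, and 5 years of follow-up". It adds that these analyses wait until study closure. *Outcomes {12}* lists direct and indirect costs at 1 year, most patient-reported and functional outcomes at 2 years, and adverse events, imaging outcomes and mortality at 5 years. Adverse events are graded 1 to 4, and grade 4 is death from complications (*Adverse event reporting and harms {22}*).

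**Missing data.** Section {20c} separates participants who actively leave (case 1) from a second group (case 2): "the participant has died or does not show up on follow-ups for unclear reasons". Two rules follow for case 2. The first is limited to the living: "In case 2, information about living participants will be retrieved from the medical records, radiographs, and the Swedish patient registry". The second has no such limit: "In case 2, missing PROMs will be imputed using multiple imputation". For case 1, no data are retrieved from other sources.

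**The concern.** The set is defined by events at 2 and 5 years, but some outcomes are complete at 1 year. Because the analyses wait until the study closes, later deaths and withdrawals will be known by then. An analyst following the text would leave out of a 1-year analysis patients whose 1-year data are on file, because of something that happened afterwards. Survival and retention are post-randomisation events, so selecting on them can distort the comparison if they differ by arm. At the least, it discards observed data.

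For two 5-year endpoints the rule fails outright. A set of patients alive at 5 years contains no deaths, so it cannot yield 5-year mortality. It also cannot contain a grade 4 adverse event, and it drops the non-fatal adverse events of everyone who died.

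The imputation sentence adds a smaller inconsistency. Case 2 names participants who have died, and the sentence on imputing patient-reported outcomes does not exclude them, although {20a} does.

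**Working it through.** **Inputs.** From *Sample size {14}*: 300 planned, five-year mortality 16.3%, a further 5% lost to dropout and emigration, 236 analysable, reoperation 3.5% and 7.4%, margin 5 percentage points, power 86%. The protocol gives no mortality at 1 or 2 years, so the timing of deaths is an assumption here.

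**The plan's own figures.**
- Analysable patients: 300 × (1 − 0.163 − 0.05) = 236.1, against 236 stated.
- Power with 118 per arm and one-sided 0.025: standard error = √[(0.035 × 0.965 + 0.074 × 0.926)/118] = 0.0294. The distance to the margin is 0.05 + 0.039 = 0.089, and 0.089/0.0294 − 1.96 ≈ 1.06, which gives 85.6%.
- A simulation of the described rerandomisation test (without blocking on sex) gave 85.9%, against 86% stated.

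Both figures reproduce.

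**Deaths by time.** Under a constant hazard, cumulative mortality at year t is 1 − 0.837^(t/5).
- Year 1: 3.50%, or 10.5 of 300.
- Year 2: 6.87%, or 20.6 of 300.
- Year 5: 16.3%, or 48.9 of 300.

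**Patients alive at 1 year (300 − 10.5 = 289.5) but outside the set.**
- 2-year set used for 1-year outcomes: 20.6 − 10.5 = 10.1, or 3.5% of 289.5.
- Single set, alive at 5 years: 48.9 − 10.5 = 38.4, or 13.3% of 289.5.

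**Range over the timing of deaths.**

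| Assumed timing | Lost, 2-year set | Lost, 5-year set |
|---|---|---|
| Half of deaths in year 1, rest spread evenly | 6.1 (2.2%) | 24.4 (8.9%) |
| Constant hazard | 10.1 (3.5%) | 38.4 (13.3%) |
| Evenly spread over 5 years | 9.8 (3.4%) | 39.1 (13.5%) |
| None in year 1, rest spread evenly | 12.2 (4.1%) | 48.9 (16.3%) |

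These counts are before withdrawal and emigration, for which the plan allows 300 × 0.05 = 15 patients, also without timing.

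**5-year endpoints.** No timing assumption is needed. About 49 of 300 (300 × 0.163) are expected to die by year 5, and none of them can be in a set alive at 5 years. Mortality in that set is zero in both arms by construction, and so is the count of grade 4 events.

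**Imputation.** Set side by side, {20a} keeps the dead out of the analysed set, while {20c} puts them in case 2 and imputes case 2 without restriction. The restriction to living participants appears only in the retrieval sentence.

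**The case against.** The strongest reply is that naming both 2 and 5 years makes best sense as two sets, one for each main analysis time. Under a single set the 2-year condition would be redundant, since anyone alive at 5 years was alive at 2. On that reading the larger loss falls away and about 10 patients (3%) remain. Only the two cost outcomes have 1 year as their listed time point; the 1-year patient-reported analyses are additional. A condensed article might also leave a 1-year set to a fuller document. The first two remarks stand and limit the size of the point. The last does not remove it: the article states a rule for all endpoints, and neither reading of that rule gives a 1-year set or a workable set for mortality.

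A reader might infer three stronger claims that the documents do not support.
- *That quality of life would be analysed for about 49 dead patients.* The wording of {20c} covers them, but {20a} would keep such values out of any analysis at or after death, and the imputation sentence may be meant to continue the one about living participants. This is an inconsistency to tidy.
- *That dropping deaths removes the most expensive patients.* Costs are defined narrowly (surgical stay, implants, pain medication, work absence, worker compensation), and nothing shows that those who died cost more on that definition.
- *That the 1-year comparison is biased.* No mortality by arm is given. The background mentions higher 30-day mortality with fusion in the lumbar spine, which is a reason not to assume equal deaths but does not show a difference here.

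**Conclusion.** The point holds as a mismatch between one stated analysis set and the time points and endpoints it must serve. For 1-year analyses the loss is about 10 of 300 if the 2-year set is used (range about 6 to 12), or about 38 if the wording means one set alive at 5 years (range about 24 to 49). The 13% figure belongs only to the single-set reading and should not be taken as established. All these counts rest on assumed death timing and exclude withdrawals, and any bias is of unknown size and direction.

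The firmer part needs neither a choice of reading nor a timing assumption: the 5-year adverse-event comparison excludes everyone who died, and 5-year mortality cannot be estimated in survivors. The plan's sample size and power figures reproduce and are unaffected. The change should be made.

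**What to change.** In {20a}, replace the single definition with sets by outcome type:

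1. Patient-reported, functional and imaging outcomes at time t: randomised participants alive and in the study at t, for t = 1, 2 and 5 years.
2. Adverse events, mortality and 1-year costs: all randomised participants, with data up to death, or censored at exit as far as consent and the case 1 rule in {20c} allow.
3. For costs, name a method that handles censoring. Counting a participant who leaves early as having a full year's cost would understate cost.

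In {20c}, limit multiple imputation of patient-reported outcomes to participants alive at the time point, so that it agrees with {20a}.

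This takes a few sentences, one choice of method for censored costs, and a statement of how data collected before an active withdrawal may be used. It needs no additional data collection and leaves the primary sample size and power calculation as they are. Because the secondary analyses wait until study closure, it can be settled before those results are seen.

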### Interim analyses {21b}

An interim analysis regarding adverse events and harms (see the section “Adverse events reporting and harms {22}” for definitions and grading) will be performed by an independent observer when 100 participants are included. The results will be reported to the principal investigator and the accountable researchers at each center and the group will make the decision to terminate the trial if the difference in adverse events and harms between the groups is statistically significant.

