### Who will take informed consent? {26a}

The consultant spine surgeon informs the patient who is eligible for inclusion of the study and hands out the written participant information. The research personnel follows up with the consent form a few days later. In this way, the patient may take some time to deliberate and subtle coercion will be minimized.

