### Implementation {16c}

One accountable spine surgeon at each center has individual logging to REDcap and the logon process is with a two-stage verification using logging and mail code. The accountable spine surgeon implements the allocation.

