### Procedure for unblinding if needed {17b}

No procedure for unblinding will be needed as all data analyses are performed after the trial is closed.

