### Adverse event reporting and harms {22}

As reoperations due to complications and adverse events are the primary outcome, all adverse events in both groups will be recorded. The adverse events will be graded according to severity (categorical variable): grade 1, any non-life-threatening complication treated without invasive procedures; grade 2, complications requiring invasive management such as surgical, endoscopic, and endovascular procedures; grade 3, life-threatening adverse events requiring treatment in an intensive care unit; and grade 4, death as a result of complications [41].

The adverse events are reported by the senior spine surgeon to the steering committee.

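### Statistical significance of any-grade adverse events is the only stated ground for stopping at 100 patients, and the by-arm results go to the centres that recruit and reoperate

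*Protocol article*

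**What the plan says.** Section Interim analyses {21b} plans one look at adverse events and harms, which "will be performed by an independent observer when 100 participants are included". On who sees it: "The results will be reported to the principal investigator and the accountable researchers at each center". On what follows: "the group will make the decision to terminate the trial if the difference in adverse events and harms between the groups is statistically significant". No significance level, direction, test or particular adverse-event comparison is given there.

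For definitions and grading the section refers to Adverse event reporting and harms {22}. There, "all adverse events in both groups will be recorded", and the scale begins with "grade 1, any non-life-threatening complication treated without invasive procedures". Grade 2 covers complications managed surgically. The same section describes reoperations due to complications and adverse events as the primary outcome.

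Three other sections bear on the point:

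- Implementation {16c}, on the single accountable surgeon at each centre: "The accountable spine surgeon implements the allocation".
- Who will take informed consent? {26a}: "The consultant spine surgeon informs the patient who is eligible for inclusion of the study".
- Procedure for unblinding if needed {17b}: "No procedure for unblinding will be needed as all data analyses are performed after the trial is closed".

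**The concern.** There are three problems, all in what the text states.

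1. **The criterion.** Significance alone decides, across all grades and in either direction. A chance imbalance, or one confined to the lowest grade, meets it as well as a serious one. So does an excess of harms after fusion, although the trial's hypothesis favours laminectomy alone and the background section already lists implant-related risks of fusion. A stop would end the trial with a third of its patients.

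2. **The recipients.** If the trial continues, centre researchers know the aggregate harm comparison, including any early reoperations, while 200 patients remain to be enrolled. The trial is open-label and its endpoint, reoperation for any reason, is partly the surgeon's decision. Surgeons cannot avoid knowing each patient's allocation, but they can avoid knowing the running comparison. The monitoring committee (study director and main coordinator/controller) is given no part in this decision, so nothing stands between the result and the centres.

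3. **The contradiction.** The unblinding section says no procedure is needed because every analysis follows closure. The interim section plans a between-group analysis during recruitment.

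**Working it through.** **The plan's own figures.** The interim rule carries no stated error rate, so there is none to reproduce. The nearest figure is the 86% power in Sample size {14}. Analysable patients: 300 × (1 − 0.163 − 0.05) = 236.1, or 118 per arm. The standard error is √[(0.035 × 0.965 + 0.074 × 0.926)/118] = 0.0294. Power = Φ[(0.05 + 0.074 − 0.035)/0.0294 − 1.96] = Φ(1.06) ≈ 0.856. The stated power is sound and not in dispute.

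**Inputs for the interim look.** From the protocol: 100 patients at 1:1, so 50 per arm, and grades 1 to 4 all counted. Assumed, because the protocol gives no figure: a two-sided 5% level, and the adverse-event rates below.

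**Step 1: one comparison, no true difference.** False-stop probability = Σ Bin(a; 50, p) × Bin(b; 50, p), summed over all pairs (a, b) for which the test gives p < 0.05.

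| Event rate in both arms | Pooled chi-square | Fisher |
|---|---|---|
| 10% | 5.1% | 1.8% |
| 20% | 5.2% | 2.8% |
| 30% | 5.0% | 3.1% |
| 40% | 5.2% | 3.2% |

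**Step 2: several overlapping comparisons, no true difference.** Simulated with assumed shares of patients with no event / grade 1 / 2 / 3 / 4 as worst grade, chi-square at 5% each. The trial stops if any comparison is significant.

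| Assumed mix (%) | Four nested cut-offs (any, ≥2, ≥3, 4) | Any event plus each grade separately |
|---|---|---|
| 80/10/7/2/1 | 10.8% | 13.4% |
| 70/15/10/3/2 | 12.8% | 16.1% |
| 60/25/10/3/2 | 13.5% | 15.7% |
| 50/30/14/4/2 | 14.3% | 17.7% |

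The range is therefore roughly 11–18%.

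**Step 3: a real difference confined to grade 1.** Assume 10% of each arm has a higher-grade event and grade 1 alone differs. Grade 1 rates of 10% vs 20%, 25% or 30% (any grade 20% vs 30%, 35% or 40%) meet the criterion with probability 21%, 39% or 60%. These are powers under assumed true differences, not false-stop rates. They show that the criterion does not separate low-grade from serious imbalances.

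**Step 4: how much of the primary endpoint is visible.** If all reoperations at the planning rates had already occurred, the look would show 50 × 0.035 = 1.75 after laminectomy and 50 × 0.074 = 3.7 after fusion. The look is triggered by inclusion, not by completed follow-up, so the actual numbers would be smaller.

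**Step 5: who receives the results.** The interim section names accountable researchers at each centre. The implementation section names one accountable spine surgeon at each centre, who implements allocation. The shared term suggests an overlap but does not prove one. Either way, the recipients are investigators at recruiting centres.

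**The case against.** **Discretion.** The group makes the decision, so stopping need not be mechanical. Criteria for discontinuing or modifying allocated interventions {11b} separately calls for an analysis of severe adverse events to judge whether the method is harmful. This stands in part: some judgement is possible. But the interim section names no consideration other than significance and does not refer to that review.

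**Detail left to an analysis plan.** The level, test and adjustment may be fixed in a document not shown, so their absence is not itself the fault, and the 5% level used here is an assumption. The sole criterion, the all-grade scope, the recipients and the contradiction are stated in the protocol.

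**Size of the false-stop risk.** A reader might multiply five independent 5% tests and arrive at 1 − 0.95^5 ≈ 23%. The documents do not support this. The total contains its own grades, so the tests are not independent, and the text speaks of a single difference. About 5% fits that wording best; 11–18% applies only if several comparisons are made.

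**Grade 1 is not necessarily trivial.** It is defined by how the event is treated, not by its consequences. An imbalance there may matter clinically, so one cannot say that any such stop would be wrong.

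**Limited exposure of the endpoint.** Few reoperations will exist at the look, participants are unblinded anyway, and the protocol lists indications for reoperation and says they are monitored. This reduces the bias but does not remove it: the listed indications say when reoperation will be considered, which leaves discretion.

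**A strict boundary on the highest grades only.** This may look like the natural remedy, but the documents do not establish it. At two-sided p < 0.001 with 50 per arm, 10 events against 0 would be needed, and complications managed surgically would not count towards stopping. Which harms should count is for the sponsor and the independent observer.

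**Conclusion.** The point holds and should be fixed before the 100-patient look, since disclosure cannot be undone. As written, significance on adverse events of any grade, in either direction, is the only named ground for termination, and by-arm results reach the recruiting centres. At an assumed two-sided 5% level with 50 per arm, the false-stop probability is about 5% for one chi-square comparison, about 2–3% with Fisher's test, and roughly 11–18% with several overlapping grade comparisons. The last range also rests on assumed event mixes.

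Two stronger readings are not supported. The rule does not inflate the type I error of the non-inferiority test; the cost of a false stop is the loss of the trial and its power. Nor does the look reveal much of the primary endpoint. The harm is that people who enrol patients and decide on reoperations know the comparative harms; its size cannot be calculated from the documents. That these people include the allocating surgeons is a reasonable inference from the shared term, not an explicit statement. The conflict between the interim and unblinding sections is plain on the text.

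**What to change.** 1. **Recipients.** In Interim analyses {21b}, let the independent observer already named keep the by-arm results and send the principal investigator and centres only a recommendation: continue, or pause and review.
2. **Criterion.** Name one adverse-event comparison and one interim significance level in advance. Treat significance on it as guidance, weighed together with severity and the harm review in section {11b}, and not as the sole trigger. Leave the choice of harms and boundary to the sponsor and the independent observer.
3. **Consistency.** Correct Procedure for unblinding if needed {17b} to acknowledge the interim look and say who may see group-level results.

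The cost is a wording amendment, resubmitted for ethical approval as the protocol requires for any change, with no extra patients and no new role. The downside is that the centres no longer see the comparative harms directly and must rely on the observer's recommendation.

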### Methods for additional analyses (e.g., subgroup analyses) {20b}

No primary subgroup analyses are planned.

### Methods in analysis to handle protocol non-adherence and any statistical methods to handle missing data {20c}

Dropouts may be one out of two entities: (1) the participant actively leaves the study or (2) the participant has died or does not show up on follow-ups for unclear reasons. In case 1, the participant will not be part of the study anymore and data will not be retrieved from other information sources. In case 2, information about living participants will be retrieved from the medical records, radiographs, and the Swedish patient registry. In case 2, missing PROMs will be imputed using multiple imputation [44]. Reoperations, adverse events, and radiographs will not be imputed.

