### Sample size {14}

Based on data from the national Swedish spine registry on patients with CSM, reoperation was estimated to be 3.5% after stand-alone laminectomy and 7.4% after laminectomy and fusion. Five-year mortality was estimated to be 16.3% in the same population [31].

We further determined that excluding a 5% excess rate of reoperation in the laminectomy group vs laminectomy and fusion was a clinically relevant target for the study and therefore set the non-inferiority margin at 5 percentage points (pp).

With a planned sample size of 300 participants and with regard to mortality and an additional 5% loss due to dropout and emigration, we end up with 236 analyzable patients. This results in a power of 86% based on simulation using rerandomization. The reason for stopping at 300 patients was made on the calculation on how many patients it is reasonable for the four sites to include in 4–5 years. Ideally, we would have reached for 90% power but have agreed to compromise with a power over 85% if that means that we will finish the study in due time.

All statistical analyses were performed in R [32], version 4.0.5 (R Foundation for Statistical Computing, Vienna, Austria), and the R code used in the sample size calculation may be received upon request.

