## Assignment of interventions: blinding

### Who will be blinded {17a}

Trial participants will not be blinded after assignment to interventions as they have online access to their medical records by a centrally managed system. Radiographic assessment is not possible to blind.

The outcome assessors and data analysts will be blinded by using a coding system for the participants and treatment groups.

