### Plans to promote participant retention and complete follow-up {18b}

Participants that do not reply on the first set of PROMs will get two reminders by mail. If still no response, they will be approached once by telephone. If still no response, information about missing participants that have not left the study will be retrieved from the medical records, radiographs, and the Swedish patient registry.

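### The dropout rule has no partial withdrawal, so a participant who declares that they want no more visits or questionnaires can lose the primary outcome even if they would accept record follow-up

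*Protocol article*

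**What the plan says.** Section {20c} of the protocol article sorts dropouts into two kinds: "1) the participant actively leaves the study or (2) the participant has died or does not show up on follow-ups for unclear reasons".

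- For the first kind: "In case 1, the participant will not be part of the study anymore and data will not be retrieved from other information sources".
- For the second kind: "In case 2, information about living participants will be retrieved from the medical records, radiographs, and the Swedish patient registry".

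Section {18b} draws the same line for questionnaire non-responders. After two mailed reminders and one telephone call, "information about missing participants that have not left the study will be retrieved from the medical records, radiographs, and the Swedish patient registry".

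Three further statements decide what happens to an active leaver:

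- Section {20c}: "Reoperations, adverse events, and radiographs will not be imputed".
- Section {20a} restricts all endpoints to an mITT population that omits randomised patients who have died, emigrated or left the study.
- Section {17a}: "Trial participants will not be blinded after assignment to interventions".

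The primary endpoint (section {12}) is any reoperation by 5 years. The sample size (section {14}) allows, beyond mortality, for "an additional 5% loss due to dropout and emigration".

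**The concern.** The two kinds of dropout leave no place for a participant who tells the site that they want no more visits, imaging or questionnaires but would not mind their records being read. The article does not define active leaving, so a site can reasonably file that person under the first kind. The result is odd. A participant who stops answering keeps a primary outcome through sources the plan already accepts, while one who is open about stopping may lose it for the rest of the 5 years.

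The loss is complete within the plan: the later reoperation is not collected, the participant is not in the mITT set, and nothing is imputed. Participants know which operation they had, so the decision to leave may depend on arm and on result. Events are few, and the claim is non-inferiority on a risk difference, so a small number of missing events can matter.

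**Working it through.** **Inputs (protocol article).** Section {14}: 300 randomised, 5-year mortality 16.3%, a further 5% for dropout and emigration, 236 analysable, power 86%, reoperation 3.5% (laminectomy, L) and 7.4% (laminectomy with fusion, LF), margin 5 pp. Section {8}: 1:1 allocation. Section {20a}: two-sided 95% confidence interval, so one-sided 0.025.

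**1. Reproduce the plan's figures.**
- Analysable: 300 × (1 − 0.163 − 0.05) = 236.1, or 118 per arm. This matches 236.
- Standard error: √[(0.074 × 0.926 + 0.035 × 0.965)/118] = √(0.1023/118) = 0.0294.
- Power: Φ[(0.05 + 0.039)/0.0294 − 1.96] = Φ(1.06) = 85.6%. A simulation of the permutation test in section {20a}, without blocking on sex, gives 86.0%. Both agree with 86%.

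**2. Events and allowance.**
- Expected reoperations: 118 × 0.035 + 118 × 0.074 = 4.1 + 8.7 = 12.9.
- Dropout and emigration: 300 × 0.05 = 15. The share who actively leave is not stated and could be anything up to 15.

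**3. Precision at stake (upper bound).** If all 15 kept a reoperation outcome, the analysable number would be 300 × (1 − 0.163) = 251.
- Power by the same formula with 125.5 per arm: 87.6%.
- Permutation simulation with 125 per arm: 89.2%.
- The gain is 2 to 3 points at most. It cannot be reached in full, because the 15 include emigrants.

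**4. Possible shift in the estimate.** Assumptions, not in the protocol: all 15 are active leavers, 7.5 per arm, and stayers have the planned rates. Each arm then has 118 + 7.5 = 125.5 patients. The plan would estimate 3.5 − 7.4 = −3.9 pp.

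| True risk, L leavers | True risk, LF leavers | L rate | LF rate | Full difference | Shift |
|---|---|---|---|---|---|
| 3.5% | 7.4% | 3.5% | 7.4% | −3.9 pp | 0 |
| 20% | 7.4% | (4.13 + 1.5)/125.5 = 4.5% | 7.4% | −2.9 pp | +1.0 pp |
| 50% | 7.4% | (4.13 + 3.75)/125.5 = 6.3% | 7.4% | −1.1 pp | +2.8 pp |
| 3.5% | 50% | 3.5% | (8.73 + 3.75)/125.5 = 9.9% | −6.4 pp | −2.5 pp |

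Put another way, each lost reoperation beyond expectation in one arm moves that arm by 1/125.5 = 0.8 pp, so two move it by 1.6 pp.

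**5. Would the conclusion change?** Take 8 L leavers with 2 later reoperations and no loss in the LF arm.
- L rate: (4.13 + 2)/126 = 4.9%. Difference: 4.9 − 7.4 = −2.5 pp.
- Standard error: √(0.0487 × 0.9513/126 + 0.074 × 0.926/118) = 0.0308.
- Upper 95% limit: −2.5 + 1.96 × 3.08 = +3.5 pp, still below 5 pp.

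**The case against.** The strongest answer is that the plan already looks after most missing participants. Those who do not answer or do not attend are followed through records, radiographs and the registry. A reader might infer from the rule that anyone who stops visits or questionnaires loses the reoperation outcome. The article does not say that: only someone recorded as actively leaving is affected, and no section says that declining visits counts as leaving. This stands, and it limits the point to participants who declare that they are stopping.

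Second, not searching the records of someone who has withdrawn consent is a proper rule. This also stands, and the fix keeps it for full withdrawal.

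Third, this is a condensed article and the consent pages are not shown, so levels of withdrawal may be set elsewhere. That is possible. But the article does more than stay silent: it states an explicit rule for everyone who actively leaves, and if finer levels exist the rule as printed contradicts them.

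Fourth, the sizes rest on chosen inputs. The 5% mixes dropout with emigration, the leavers' risks are assumed, and the fusion arm could lose as many events or more. A reader might infer that the rule favours laminectomy, or that it uses up a set share of the margin. The documents support neither: the sign can go either way, and in the one-arm example the upper limit stays below 5 pp.

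Fifth, lost events could be bounded in a sensitivity analysis. True, but a bound is weaker than data that the plan's own sources could supply.

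**Conclusion.** The concern holds in limited form. The rule as written makes active leaving all or nothing, and together with the mITT definition and the absence of imputation it can remove the primary outcome of participants who would have allowed record follow-up.

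The effect on precision is small: at most 236 to 251 analysable and 86% to about 88–89% power, on the unattainable assumption that the whole 5% could be kept. The effect on bias is unknown in size and direction. With about 13 expected events, shifts of 1 pp or more either way follow from plausible but assumed risks among up to 15 leavers. No scenario worked here changes the non-inferiority conclusion at the planned rates.

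It might also be inferred that registers would supply deaths among leavers. The article names only the Swedish patient registry and gives no source for death, so that cannot be claimed. This is a cheap improvement worth making while enrolment is open, since data not collected after withdrawal may not be recoverable later. It is not a demonstrated error in the result.

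**What to change.** In section {20c}, divide the first kind of dropout into two levels, put to the participant at withdrawal and described in the consent form:

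- **(a)** The participant stops visits, imaging and questionnaires, but allows continued capture of reoperations and adverse events from medical records and the Swedish patient registry, and of death where those sources show it.
- **(b)** The participant withdraws permission for any further data.

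Apply the no-retrieval rule to (b) only, and align section {18b}. State in section {20a} that level (a) participants have not left the study and stay in the primary analysis set; without that sentence the retrieved reoperations would never reach the primary analysis. Record the level, date and reason, and report the counts of each level by arm.

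The cost is an amendment to the consent and withdrawal forms with ethics resubmission, for which section {25} already gives the route. Participants already enrolled need be asked only if they withdraw. The sources are those already planned for non-attenders.
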